### Study design

2.1.

In this prospective, multi-center, double-blind, randomized sham-controlled, superiority trial, the effectiveness of low-frequency rTMS over the contralesional M1 will be compared to that of sham rTMS in patients who require upper limb rehabilitation due to subcortical and brainstem ischemic stroke.

Patients admitted with acute stroke will be recruited from the rehabilitation ward. Eligibility will be screened by the research team and the patients will be randomly allocated to the intervention group (real rTMS) or control group (sham rTMS) in a 1:1 ratio, with stratification into two subgroups according to the baseline Upper Extremities Fugl-Meyer Assessment (UE-FMA) score. The baseline evaluation (T0) will be performed by a blinded evaluator after group allocation. All participants will receive 30 min of intervention (real rTMS in the intervention group and sham rTMS in the control group), accompanied by 30 min of occupational therapy (OT) after the intervention. The intervention will be provided to participants for 10 consecutive working days. All participants will receive the same amount of occupational and physical therapy (PT) consisting of two sessions of 30-min OT and PT daily during this period. The evaluation will be performed at the end of the intervention period (T1) and 4 weeks after the end of the intervention (T2). The doses of OT and PT will be monitored and documented by the patient/caregiver at T1 and T2. An overview of the study design and process is shown in Figure 1.

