##### Implementation of occupational therapy

2.4.1.1.

OT will be provided twice a day for 30 min each, starting within 10 min after rTMS in both the intervention and control groups between T0 and T1. Participants will receive one-on-one OT with an occupational therapist, comprising task-oriented therapy, including shaping exercises. The difficulty will be tailored to each participant and will be gradually increased according to the improvement in the motor function of the paralyzed hand. Therapists will be blinded to the participant groups throughout the trial. Participants will be provided with a rehabilitation diary, and the therapy dosage will be recorded during the period between T1 and T2. In the rehabilitation diary, the date and duration of rehabilitation treatment in minutes will be recorded as items of occupational therapy, physical therapy, or other treatment.

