#### Primary outcome measure

2.5.1.

Primary outcome is the amount of change in the number of Box and Block Test (BBT) (17) at T2 compared to that at T0 (3, 5, 13, 18). The BBT is a manual dexterity test that has been used to evaluate physically disabled individuals. The BBT consists of a partition and wooden box divided into two compartments containing 150 blocks. Participants will be asked to move as much as possible, one at a time, from one compartment of the box to another of the same size, within 60 s. The BBT score is the number of blocks the participant has moved (17).

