#### Analysis of primary outcome

2.8.3.

Descriptive statistics (number of participants, mean, standard deviation, median, minimum, and maximum) of the BBT values at T0 and T2 and the degree of BBT change between T0 and T2 will be presented by group. The statistical significance of BBT changes between groups will be confirmed by analysis of covariance (ANCOVA) with the number of BBTs at T0 and stratified variables (depending on whether the UE-FMA score is less than 28 points) and occupational therapy dosage between T1 and T2 as covariates. Additionally, in the subgroup analysis, the location of stroke lesions will also be included as a covariate in the ANCOVA. All statistical analysis will be performed with significance level of 0.05.

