#### Analysis of secondary outcome

2.8.4.

Descriptive statistics (number of participants, mean, standard deviation, median, minimum, and maximum) for BBT values at T0 and T1 and the degree of BBT changes between T0 and T1 will be presented by group. The statistical significance of BBT changes between groups will be confirmed by analysis of covariance (ANCOVA) analysis with number of BBTs at T0 and stratified variables (depending on whether the UE-FMA score is less than 28 points) as covariates.

For other secondary outcomes (UE-FMA score, K-MBI, NIHSS, FTT score, Brunnstrom Stage, Grip strength), descriptive statistics (number of participants, mean, standard deviation, median, minimum, and maximum) at T0, T1, and T2 will be presented for each group. The statistical significance of BBT changes between T0 and T1 and T0 to T2 between groups will be confirmed by ANCOVA with the number of BBTs at T0 and stratified variables (depending on whether the UE-FMA score was less than 28 points) and occupational therapy dosage during the corresponding period as covariates. Additionally, in the subgroup analysis, the location of stroke lesions will be included as a covariate in the ANCOVA. All statistical analysis will be performed with significance level of 0.05.

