## Discussion

3.

This study was designed as a multi-center, double-blind, randomized sham-controlled trial that aims to confirm the efficacy of low-frequency contralesional rTMS in the recovery of upper limb motor function in patients with subcortical or brainstem ischemic stroke. To ensure the rigor of the investigation, the participants will be stratified into two subgroups based on their initial severity. Moreover, the amount of OT and PT will be the same in the intervention and control groups during the intervention period, and the amount of total therapy will be recorded throughout the trial. By controlling and recording the potential cofounders of the motor recovery after stroke, the study results are anticipated to report high-quality evidence on the effectiveness of rTMS on motor recovery after stroke.

In this study, among various rTMS protocols, low frequency rTMS over the contralesional M1 will be applied in attempts to normalize imbalance of IHI by suppressing the over-inhibition of contralesional M1 toward ipsilesional M1 (9). In previous studies, low-frequency rTMS was often chosen over high-frequency rTMS because of the low risk of seizures in the healthy corticospinal system and its minimal effect on motor behavior (8, 10). However, previous results regarding the efficacy of low-frequency rTMS over the contralesional M1 for motor recovery in patients with acute and subacute stroke remain inconsistent. Khedr et al. (24) reported that low-frequency rTMS is more advantageous in recovering upper extremity function after stroke compared to high-frequency rTMS. Dafotakis et al. (29) also reported the possible beneficial effects of low-frequency rTMS on hand function recovery in patients with acute and subacute subcortical stroke. In contrast, other studies have reported no significant beneficial effects of low-frequency rTMS compared with sham rTMS (30, 31). In a meta-analysis, Hsu et al. (11) confirmed the effect of low-frequency rTMS on the recovery of upper extremity function in patients with stroke and reiterated the notion that post-stroke hemisphere competition is altered and that this imbalance can be resolved by reducing the cortical excitability of unaffected hemispheres through low-frequency rTMS.

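### The primary ANCOVA adjusts for occupational therapy received after the rTMS course has ended, so it need not estimate the overall T0–T2 effect that the trial is designed to test

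*Protocol article*

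**What the plan says.** All references are to the protocol article.

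- Section 2.5.1 defines the endpoint: "Primary outcome is the amount of change in the number of Box and Block Test (BBT) (17) at T2 compared to that at T0".
- Section 2.8.3 tests it by "analysis of covariance (ANCOVA) with the number of BBTs at T0 and stratified variables" (UE-FMA below 28 or not) "and occupational therapy dosage between T1 and T2 as covariates". No primary test without the dosage term is described.
- Section 2.1 places T1 at the end of the intervention and T2 four weeks later.
- Therapy is held equal only up to T1. In the Discussion's words, "the amount of OT and PT will be the same in the intervention and control groups during the intervention period". After T1 it is only observed (section 2.4.1.1): "Participants will be provided with a rehabilitation diary, and the therapy dosage will be recorded during the period between T1 and T2".
- The Discussion gives the reason: "By controlling and recording the potential cofounders of the motor recovery after stroke".
- Section 2.8.4 repeats the term for the secondary outcomes other than T0–T1 BBT, as "occupational therapy dosage during the corresponding period as covariates". The T0–T1 BBT analysis in the same section uses baseline BBT and stratum only.

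**The concern.** The primary hypothesis (section 2.8.1) and the sample size (section 2.6) both concern the whole difference between arms in T0–T2 change. That difference includes whatever rTMS does by way of later therapy use.

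Occupational therapy after T1 may respond to recovery by T1. A patient who has recovered well may be discharged and need less therapy, or may be able to do more. Dosage is then partly a consequence of treatment, and holding it constant takes out that part of the effect. It may also share unmeasured causes with recovery, such as motivation or general health. Conditioning on it then makes patients with equal dosage in the two arms unlike each other in those causes.

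A confounder of a treatment comparison must influence allocation. Here allocation is random and precedes the dosage, so the stated rationale does not apply to the contrast between arms. This is the single confirmatory test, and section 2.8.4.1 rests the final evaluation on it in the full analysis set.

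**Working it through.** **1. The plan's own figure.** The inputs in section 2.6 are a difference of 17.40 − 10.90 = 6.50 blocks, SD 10.30, 5% significance and 80% power. Two-sided, n per group = 2 × (1.960 + 0.842)² × 10.30² / 6.50² = 39.4, so 40. Adding 10% gives 40 × 1.10 = 44 per group, 88 in total. The stated size is reproduced. The calculation compares mean change between arms and makes no use of dosage.

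**2. What the adjusted model estimates.** Express dosage D in within-arm SD units. Let *a* be the shift in mean dosage caused by arm. Let *k* be the within-arm slope of BBT change on dosage, in blocks per SD. The slope has two parts, k = b + c·g:
- b is the direct effect of dosage on BBT change;
- c is the loading of a shared unmeasured cause on dosage, and g its loading on BBT change.

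In this linear model:

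adjusted coefficient = total effect − a·k

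The bias is therefore zero if a = 0 or k = 0. A large simulated sample (400,000) agreed with this formula.

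**3. Assumed inputs.** The document gives no dosage figures. Take *a* = ±0.3 or ±0.5 SD, and *k* from −2 to 4. For example, b = 2 with c·g = 0.4 × 5 = 2 gives k = 4; b = 0 with c·g = −0.4 × 5 gives k = −2. Fix the total effect at 6.5, the within-arm SD of BBT change at 10.3, and 40 per arm. Gains from baseline BBT are left out.

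**4. Power.** The residual SD is s = √(10.3² − k²). The standard error is s × √(2/40) × √(1 + a²/4), where the last factor reflects the correlation of dosage with arm. Worked for a = 0.5, k = 4:
- estimate = 6.5 − 0.5 × 4 = 4.5
- s = √(106.09 − 16) = 9.49
- SE = 9.49 × 0.2236 × 1.031 = 2.19
- ratio = 4.5 / 2.19 = 2.06; power by the noncentral t with 77 df = 53%

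| a (SD) | k (blocks per SD) | Adjusted estimate | Power |
|---|---|---|---|
| 0 | 0 | 6.5 | 80% |
| 0 | 4 | 6.5 | 86% |
| 0.5 | 0 | 6.5 | 77% |
| 0.3 | 3 | 5.6 | 70% |
| 0.5 | 3 | 5.0 | 59% |
| 0.5 | 4 | 4.5 | 53% |
| −0.5 | −2 | 5.5 | 65% |
| 0.5 | −2 | 7.5 | 89% |
| −0.5 | 3 | 8.0 | 94% |
| −0.5 | 4 | 8.5 | 97% |

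Simulated trials of 40 per arm at the extremes gave means of 4.5 and 8.5, with rejection of 53% and 97%.

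**5. After the change.** Without the dosage term the arm coefficient targets the total effect of 6.5 whatever *a* and *k* are. The sample size stays at 40 per group, 88 in total.

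**The case against.** **The covariate has a purpose.** The Introduction cites variation in occupational therapy between studies as a proposed reason for an earlier null meta-analysis, and the authors want therapy amount under control. If dosage is unrelated to arm, including it costs nothing in bias and can gain precision (86% against 80% power at k = 4). That is so, but the benefit depends on dosage not responding to treatment, and reporting dosage by arm meets the same purpose.

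**Blinding limits the problem.** Participants, evaluators and therapists are blinded (section 2.3), so dosage should rarely change because someone knows the allocation. This stands for that route. It does not stop dosage from following recovery.

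**The bias would mostly be towards no effect.** If rTMS and latent recovery move dosage in the same direction, the settings above give 4.5 to 6.5 blocks, so attenuation or no bias. The 8.5 needs rTMS to lower dosage while better latent recovery raises it. This is a fair limit on the upper end. An upward error is still possible without that conflict. If better recovery lowers dosage (a = −0.5, c = −0.5, g = 5) and therapy itself helps (b = 3), then k = 3 − 2.5 = 0.5 and the estimate is 6.5 + 0.25 = 6.75, though here the error is small.

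**Stronger readings that the document does not support.**
- A reader might infer that the type I error is generally inflated. If rTMS does nothing, recovery cannot carry an effect of arm to dosage. Then a = 0 and the test keeps its level (4.6% to 5.3% in simulation). Rejection of up to about 15% appears only if the total effect is set to zero while rTMS still moves dosage. That needs another route, or effects that cancel exactly.
- A reader might infer that the needed assumption cannot be checked. It can: dosage is recorded in minutes and can be compared by arm. The check is weak, since 40 per arm has only about 26% power for a 0.3 SD difference.
- A reader might infer that participants without a diary leave the primary model. The article states no complete-case rule, and such handling is commonly left to an analysis plan that is not shown.
- A reader might infer that the randomised contrast is lost. Section 2.8.3 presents BBT change descriptively by group, so it can be recovered, but it is not the planned test.

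**Conclusion.** The primary model is wrong as written. It conditions on a variable that arises after randomisation and after the full intervention, and the reason given, control of confounding, does not apply to a randomised contrast. The estimate then need not be the total T0–T2 effect named in the hypothesis and used for the sample size.

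The size is unknown because the document has no dosage data. Under the assumed inputs, a true 6.5 blocks would be estimated at about 4.5 to 8.5, which is 2.0 / 6.5 = 31% either way, with power of about 53% to 97%. The bias is zero if dosage does not differ by arm or is unrelated to outcome within arm. The conclusion about what the model targets does not depend on these inputs; the magnitudes do, and are illustrative only.

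**What to change.** - In section 2.8.3, remove T1–T2 occupational therapy dosage from the primary ANCOVA. Base the conclusion on pre-randomisation covariates only: T0 BBT and UE-FMA stratum. Institution may be added, since section 2.3 randomises within institution, but the point does not depend on it.
- In section 2.8.4, make the same change to the corresponding-period dosage term for the other secondary outcomes. The T0–T1 BBT analysis already omits it.
- Report therapy dosage by group for each period.
- Keep any dosage-adjusted model as a labelled sensitivity analysis that does not drive the conclusion, stating the assumption it needs.

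The cost is a change of one sentence in each of the two sections, made before unblinding. No extra data or participants are needed.

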#### Analysis of secondary outcome

2.8.4.

Descriptive statistics (number of participants, mean, standard deviation, median, minimum, and maximum) for BBT values at T0 and T1 and the degree of BBT changes between T0 and T1 will be presented by group. The statistical significance of BBT changes between groups will be confirmed by analysis of covariance (ANCOVA) analysis with number of BBTs at T0 and stratified variables (depending on whether the UE-FMA score is less than 28 points) as covariates.

For other secondary outcomes (UE-FMA score, K-MBI, NIHSS, FTT score, Brunnstrom Stage, Grip strength), descriptive statistics (number of participants, mean, standard deviation, median, minimum, and maximum) at T0, T1, and T2 will be presented for each group. The statistical significance of BBT changes between T0 and T1 and T0 to T2 between groups will be confirmed by ANCOVA with the number of BBTs at T0 and stratified variables (depending on whether the UE-FMA score was less than 28 points) and occupational therapy dosage during the corresponding period as covariates. Additionally, in the subgroup analysis, the location of stroke lesions will be included as a covariate in the ANCOVA. All statistical analysis will be performed with significance level of 0.05.

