Research on the effectiveness of rTMS remains controversial. Hsu et al. (11) performed a meta-analysis of 34 existing studies in 2012 and confirmed the significant effects of rTMS on upper limb motor function recovery in patients with stroke. In contrast, Graef et al. (4) investigated the effects of rTMS combined with upper limb training vs. sham rTMS combined with upper limb training on upper limb recovery after stroke in 2016 and concluded that there were no significant differences between groups. Harvey et al. (12) reported a clinical study comparing the effects of rTMS and sham rTMS on the functional recovery of the upper extremities of stroke patients in 2018, and found no difference between the rTMS and sham rTMS groups. Therefore, it is unclear whether rTMS affects the recovery of upper limb function in patients with stroke. Harvey et al. (12) suggested that no significant effect was confirmed because the effect of rTMS may vary depending on the location or severity of the stroke. Graef et al. (4) suggested that the heterogeneity of occupational therapy between studies was the reason why a significant effect of rTMS was not confirmed in the meta-analysis.

Kim et al. (13) conducted a randomized controlled trial to determine the efficacy of low-frequency rTMS on the contralateral M1 combined with occupational therapy in patients with stroke. Although the study did not show a significant difference between the rTMS and sham groups, subgroup analysis based on cortical involvement revealed that low frequency rTMS on contralesional M1 led to improvements in the Brunnstrom stage of hand function in the group without cortical involvement. This result led us to hypothesize that the type and location of stroke may affect the efficacy of rTMS warranting further investigation.

Therefore, a multicenter randomized controlled trial has been designed to confirm the effectiveness of low-frequency rTMS over the contralesional M1 in patients with subcortical and brainstem ischemic stroke.

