### Randomization and blinding

2.3.

A list of random assignments will be prepared by a statistician who is independent of the research team. Within each institution, the participants will be stratified into two subgroups based on a baseline UE-FMA score of 28 using a stratified block randomization method with blocks of size 2 within each stratum, and the assignment ratio of the intervention and control groups will be maintained at 1:1. A random assignment list will be generated using SPSS version 23.0(IBM Corp., Armonk, NY, United States). The block size and seed number used will be randomly selected by a statistician responsible for the random assignment. Random assignments will be stored in opaque envelopes for each participant and delivered to the coordinator at the start of the intervention.

This clinical trial will be performed in a double (participant and evaluator) blind-fold manner, and the therapists who perform the treatment will also be blinded throughout the study. Owing to the nature of this clinical trial, the investigator who will perform rTMS will not be blinded to the assigned group.

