### Sample size

2.6.

According to a previous study (13), the average change in BBT at 1 month after baseline was confirmed to be 17.40 (9.80) in subcortical and brainstem stroke subjects who underwent rTMS and 10.90 (10.30) in subjects who received sham stimulation. The average change in BBT in the intervention and control groups in this clinical trial is also expected to be similar, and the standard deviation is assumed to be a large value of 10.30 for the conservatively setting. Assuming a significance level of 5% and a power of 80% under a BBT average change of 6.50 (intervention group: 17.40, control group: 10.90) and a standard deviation of 10.30, the number of subjects calculated is at least 40 per group; therefore, a total of 88 subjects will be recruited, considering a 10% dropout rate.

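### Brunnstrom stage, an ordered scale, is to be summarised and tested as if interval-scaled; the ANCOVA is valid, but an ordinal model is easier to interpret and can have more power

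*Protocol article*

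**What the plan says.** Section 2.8.4 of the protocol article (Analysis of secondary outcome) puts Brunnstrom stage in one list with scores, counts and strength measurements: "For other secondary outcomes (UE-FMA score, K-MBI, NIHSS, FTT score, Brunnstrom Stage, Grip strength), descriptive statistics" follow for T0, T1 and T2, namely number, mean, SD, median, minimum and maximum.

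The next sentence covers changes over two intervals, the second being "T0 to T2 between groups will be confirmed by ANCOVA". Its literal subject is change in BBT. The covariates are BBT at T0, the UE-FMA stratum and the occupational therapy dose in the period. Section 2.5.2 defines the Brunnstrom outcome as change from T0 at T1 and at T2, so ANCOVA of Brunnstrom change is the natural reading.

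No ordinal or rank method is named for any efficacy outcome. The Wilcoxon fallback in section 2.8.2 applies to baseline comparisons only.

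The Introduction says of a previous trial that "low frequency rTMS on contralesional M1 led to improvements in the Brunnstrom stage of hand function in the group without cortical involvement", and that this result led to the present hypothesis about stroke type and location.

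**The concern.** A stage is an ordered category. A linear model of change takes every step as equally large and the residual variance as constant. It reports a mean difference in stages, which has no plain meaning. As an illustration, a difference of 0.30 stages arises if 30% more patients gain one stage (0.30 × 1) or if 15% more gain two (0.15 × 2).

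A ceiling may add to the problem. Entry requires UE-FMA above 15 with no upper limit (section 2.2), and the Discussion expects some patients to be mild enough for UE-FMA to show a ceiling. If many patients reach the top stage, the linear model may be a weaker test than one built for ordered categories.

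At stake is the clarity, and possibly some of the power, of one secondary result. Readers will look for that result because the Introduction ties the hypothesis to it.

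**Working it through.** **The plan's own figure.** The only sample size is for BBT: "Assuming a significance level of 5% and a power of 80% under a BBT average change of 6.50" ("intervention group: 17.40, control group: 10.90"), with "a standard deviation of 10.30, the number of subjects calculated is at least 40 per group". Sidedness is not stated; two-sided reproduces the figure:

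n per group = 2 × (1.960 + 0.842)² × 10.30² / 6.50² = 2 × 7.85 × 106.09 / 42.25 = 39.4, so 40.

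An exact t-test gives 40.4, with power 0.796 at 40. Adding 10% gives 40 × 1.1 = 44 per group, hence "a total of 88 subjects will be recruited, considering a 10% dropout rate". (Dividing by 0.9 would give 45 per group, 90 in total.) None of this rests on Brunnstrom stage. It does set the size for the check: 40 analysed per arm, with 1:1 allocation.

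**Inputs the documents do not give.** The number of stages, their distribution, any ceiling and the treatment effect are all assumed here: six stages with 2 to 6 occupied, a log odds ratio of 1.2 (e^1.2 = 3.3), and 9% to 66% of controls at the top stage at follow-up.

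**Models compared**, both with own baseline stage b, UE-FMA stratum s and treatment t. Institution and therapy dose were left out.

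- ANCOVA of change: (y − b) = α + βb + γs + τt + error, t-test of τ.
- Proportional odds on follow-up stage: logit P(y ≥ k) = −θ_k + βb + γs + δt, likelihood-ratio test of δ; e^δ is the common odds ratio.

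**Results at the nominal 5% level**, 1,500 replicates per scenario:

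| Mechanism | Controls at top stage | ANCOVA | Prop. odds | Gap (points) |
|---|---|---|---|---|
| Proportional odds true | 9% | 0.730 | 0.765 | 3.5 |
| | 18% | 0.743 | 0.777 | 3.4 |
| | 31% | 0.715 | 0.754 | 3.9 |
| | 46% | 0.621 | 0.698 | 7.7 |
| | 66% | 0.431 | 0.547 | 11.6 |
| Normal latent errors | 19% | 0.714 | 0.738 | 2.4 |
| | 47% | 0.565 | 0.635 | 7.0 |
| Effect only in more severe patients | 18% | 0.746 | 0.751 | 0.5 |
| | 31% | 0.780 | 0.773 | −0.7 |
| | 47% | 0.770 | 0.779 | 0.9 |

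With no effect, ANCOVA rejected in 4.2% to 5.9% of trials and the likelihood-ratio test in 5.7% to 6.9%. Monte Carlo error is about 1.2 points on power and 0.6 on type I error.

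**Allowing for the liberal test.** Part of each gap comes from that excess. Further simulations, also with 40 per arm and assumed distributions, compared the tests at equal true size. Differences are proportional odds minus ANCOVA:

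- Stage gains with a cap at the top: about +6 to +10 points in one set. In another (700 replicates; 5%, 20% and 35% at the top) raw gaps of about 5, 8 and 10 shrank to about 2, 5 and 7.
- Effect in milder patients: about +9 to +12.
- Normal latent errors: about −2 to +4.
- Effect confined to severe patients: about −10 to +3.

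Across all runs the likelihood-ratio test had a size of about 5% to 8%.

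**The case against.** The strongest reply is that this is largely preference. ANCOVA holds its type I error, the outcome is secondary, no sample size depends on it, and the median and range are already planned beside mean and SD. All of that stands and limits the weight of the point. A reply that model choice may be left to an unseen analysis plan is weaker, because the article does name a method.

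The article also never literally prescribes ANCOVA of Brunnstrom change, since the sentence names BBT. That wording is the firmer defect and should be corrected first. Correcting it alone would still leave a stage scale analysed as interval data.

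The ceiling is assumed: the Discussion states one for UE-FMA only, and recruits are rehabilitation-ward patients. Nor does ANCOVA simply count a patient with no room to improve as a non-responder. Moving b to the right-hand side gives y = α + (β + 1)b + γs + τt + error with the same τ, so a lower expected gain at high baseline is partly adjusted for.

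A reader might infer that Brunnstrom stage was the only outcome to improve in the earlier trial. The documents do not say so. The Discussion reports upper-extremity recovery more generally from that study, and section 2.6 takes the 6.50-block BBT difference from it.

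**Conclusion.** The point holds as a modest improvement to one secondary outcome. An ordered scale that the Introduction names as motivating the hypothesis is summarised by mean and SD and, on the natural reading, tested by ANCOVA of change. The test is valid, but its estimate is hard to interpret and it can cost power: roughly 0 to 12 points, most with a ceiling or an effect in milder patients. The Discussion's expectation that rTMS may work less well in severe paralysis makes the latter plausible.

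A reader might conclude that proportional odds is always better. The results do not support that: there was little or no loss, and in some runs an advantage for ANCOVA, when the effect was confined to severe patients. Every power figure rests on stage distributions and effects that the documents do not give. The primary analysis and the 88-patient sample size are untouched.

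**What to change.** In section 2.8.4:

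1. Correct the BBT wording so that each outcome is tested on its own change and adjusted for its own baseline.
2. Analyse Brunnstrom stage at T1 and at T2 by proportional-odds regression with treatment, baseline stage and the stratification factors (UE-FMA stratum and institution, as in section 2.3).
3. Report the common odds ratio with its 95% CI, and counts per stage by arm at each visit.
4. Keep the ANCOVA as a sensitivity analysis.

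Whether therapy dose belongs in the model is a separate question that this change does not settle.

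The cost is about one paragraph of wording before database lock, with no new data. There are two downsides: the proportional-odds assumption needs a check, and the likelihood-ratio test is slightly liberal at about 80 patients (about 5% to 8% in simulation).

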#### Secondary outcome measures

2.5.2.

Several secondary outcome measures will be assessed (Table 2), including: changes in the number of BBT at T1 compared to those at T0; UE-FMA (19) score changes at T1 and T2 compared to those at T0 (3, 13, 20); changes in the Korean version of Modified Bartherl Index (K-MBI) (21) score at T1and T2 compared to those at T0 (13, 22); changes in the NIH Stroke Scale (NIHSS) scores (23) at T1 and T2 compared to those at T0 (12, 13, 24); the finger tapping test (FTT) (25) (participants tap their index fingers as quickly as possible within a 10-s time interval, and the number of times they tap their fingers becomes an FFT score) score changes at T1and T2 compared to those at T0 (13, 24); the Brunnstrom Stage (26) changes at T1and T2 compared to those at T0 (13); the Modified Ashworth Scale (MAS) score changes at T1and T2 compared to those at T0 (13, 22, 27); and the degree of change in grip strength (hand grip, pinch grip, lateral pr, and three-jaw chuck) measured using the JAMAR dynamometer (Performance Health Supply Inc., Cedarburg, United States) at T1 and T2 compared to that at T0 (3, 13, 22).

**Table 2 tab2:** Timetable and measures to be made.

	Intervention period		4 weeks after EOT (T2)
	Baseline (T0)	EOT (T1)	

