**Secondary outcome measures**			
Upper extremity FMA	√	√	√
K-MBI	√	√	√
NIHSS	√	√	√
Finger Tapping Test	√	√	√
Brunnstrom stage	√	√	√
Modified Ashworth scale	√	√	√
Grip strength	√	√	√

EOT, end-of-treatment; FMA, Fugl-Meyer Assessment; K-MBI, Korean version of the Modified Barthel Index; NIHSS, National Institutes of Health Stroke Scale.

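### As written, section 2.8.4 tests only BBT change under the other secondary outcomes, and the Modified Ashworth Scale is missing from the analysis section

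*Protocol article*

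**What the plan says.** Section 2.5.2 of the Protocol article defines the secondary outcomes. They are BBT change at T1, and changes at T1 and T2 from T0 in seven other measures: UE-FMA, K-MBI, NIHSS, finger tapping test (FTT), Brunnstrom stage, MAS and grip strength. On MAS it says "the Modified Ashworth Scale (MAS) score changes at T1and T2 compared to those at T0". Table 2 schedules "Modified Ashworth scale" at all three time points, and the Abstract lists it too.

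Section 2.8.4 has two paragraphs. The first covers BBT change from T0 to T1 and gives this model: "ANCOVA) analysis with number of BBTs at T0 and stratified variables (depending on whether the UE-FMA score is less than 28 points) as covariates". The second opens with "For other secondary outcomes (UE-FMA score, K-MBI, NIHSS, FTT score, Brunnstrom Stage, Grip strength), descriptive statistics" and then states one between-group test: "BBT changes between T0 and T1 and T0 to T2 between groups will be confirmed by ANCOVA with the number of BBTs at T0". The further covariates are the UE-FMA stratum and "occupational therapy dosage during the corresponding period as covariates". On the level of the tests: "All statistical analysis will be performed with significance level of 0.05".

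**The concern.** The second paragraph of section 2.8.4 is the only place that could say how the non-BBT secondary outcomes are compared between groups, and the variable it names is the wrong one. A statistician who follows the sentence has no dependent variable and no baseline covariate for any of these outcomes. The same sentence gives BBT a second analysis at both time points. That leaves two models for one question at T1, and nothing in the text says which one counts. MAS is absent from a list that names its outcomes one by one.

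The stake is pre-specification. The article is the public record of what was planned. If the correct model is settled only once data are visible, the choice of baseline covariate, therapy-dosage adjustment and method for MAS can no longer be shown to be independent of the results.

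**Working it through.** The plan gives no figure on this point, so the check sets the sections side by side.

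**Step 1: outcomes defined against outcomes analysed.**

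| Secondary outcome | Defined in 2.5.2 and Table 2 | Named in 2.8.4, second paragraph | Test stated on its own change with its own T0 value |
|---|---|---|---|
| UE-FMA | yes | yes | no |
| K-MBI | yes | yes | no |
| NIHSS | yes | yes | no |
| FTT | yes | yes | no |
| Brunnstrom stage | yes | yes | no |
| Grip strength | yes | yes | no |
| MAS | yes | no | no |

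Seven are defined, six are named, and none has its own test. The six named outcomes do get summary statistics by group at T0, T1 and T2. MAS gets neither a summary nor a test anywhere in section 2.8.

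**Step 2: BBT models on the literal reading.**

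| Comparison | Where | Covariates |
|---|---|---|
| BBT T0 to T1 | 2.8.4, first paragraph | T0 BBT, UE-FMA stratum |
| BBT T0 to T1 | 2.8.4, second paragraph | T0 BBT, UE-FMA stratum, therapy dosage in the matching period |
| BBT T0 to T2 (primary) | 2.8.3 | T0 BBT, UE-FMA stratum, therapy dosage from T1 to T2 |
| BBT T0 to T2 (repeat) | 2.8.4, second paragraph | T0 BBT, UE-FMA stratum, therapy dosage in the matching period |

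The two T0 to T1 models differ by one covariate. The two T0 to T2 models describe the dosage covariate differently, so they need not give the same result.

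**Step 3: is the intended analysis stated elsewhere?** No section names the change in UE-FMA, K-MBI, NIHSS, FTT, Brunnstrom stage or grip strength as a dependent variable of a test, or the T0 value of any of them as its covariate. Section 2.5.2 comes closest, since it defines each outcome as a change from T0, but it gives no model.

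**Step 4: what is not affected.** The sample size in section 2.6 rests on BBT alone. With a difference of 6.50, SD 10.30, two-sided 5% and 80% power, n = 2 × (1.960 + 0.842)² × 10.30² / 6.50² = 2 × 7.85 × 106.09 / 42.25 ≈ 39.4, so 40 per group. Adding 10% gives 44 per group and 88 in total, as stated. Correcting section 2.8.4 changes none of this, and it leaves the primary model in section 2.8.3 as it is.

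**The case against.** The strongest reply is that this is carried-over wording. The sentence closely follows the BBT paragraphs and stands under a list of other outcomes. If one mention of BBT was carried over, so was the other. Read that way throughout, the plan means each outcome's change adjusted for its own T0 value, which is the right analysis, and the second BBT model and the repeated primary test disappear. This is probably what was intended. It softens the severity but does not remove the defect: the reader must replace two terms and add an outcome, and no other sentence confirms the result.

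A second reply is that the article is condensed and a SAP may hold the detail. That would answer an omission. Here a model is given, with dependent variable, covariates and significance level, and it names the wrong variable.

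A reader might also infer a measurable loss of precision, or bias from chance imbalance, by supposing that each outcome's change is analysed but adjusted for T0 BBT. The documents do not support that. It corrects half of the sentence and keeps the other half. It also needs correlations that the article does not give: assuming 0.5 to 0.8 between baseline and follow-up, and 0.3 to 0.7 between the outcome's baseline and BBT, residual variance would be about 6% to 30% larger. That range ignores the UE-FMA stratum, which is in the model and would absorb part of the excess, most clearly for UE-FMA itself. Any bias figure would depend on a chosen imbalance, while its expectation under randomisation is zero. I do not count either as evidence of harm.

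**Conclusion.** The analysis rule is wrong as written. The severity is moderate and the reach is secondary outcomes only. Six outcomes have no stated between-group test of their own, MAS is missing from all of section 2.8, and on the literal reading BBT is modelled twice at T1 and twice at T2. These counts rest on the article's text alone and need no assumption.

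Two stronger conclusions might be drawn, and neither is supported. One is that the sponsor does not intend to test these outcomes; defining them as changes from T0 points the other way. The other is that MAS will go unanalysed; the article shows only that its analysis section leaves MAS out, and an unseen SAP may cover it.

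**What to change.** Before unblinding, correct the second paragraph of section 2.8.4, and the SAP if it repeats the wording:

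- Make the dependent variable the change in each listed outcome from T0 to T1 and from T0 to T2.
- Make the baseline covariate the T0 value of that same outcome.
- Add MAS to the list with a stated analysis. MAS and Brunnstrom stage are ordinal, so an ordinal or rank-based method may suit them better than ANCOVA.
- Keep a single model for BBT from T0 to T1, and state no repeat test of BBT from T0 to T2.

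Whether to add institution as a covariate, or to remove therapy dosage, is a separate question that this correction need not settle. Once the wording is corrected, the other outcomes at T1 would still be adjusted for dosage while BBT at T1, under the first paragraph, would not. The sponsor should say whether that difference is deliberate.

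The cost is a change of wording. Table 2 already schedules every measure at T0, T1 and T2, so no new data, visits or participants are needed.
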